**Methods:**

A cluster randomized controlled trial (RCT) will be conducted to evaluate the effectiveness of the ITBCS compared with usual care for Chinese rural family caregivers of people with dementia. A total sample of 168 rural family caregivers will be recruited. The intervention components consist of a 3-month intensive telephone-based care support intervention followed by telephone-based follow-up consultations for 6 months. The control group will receive usual care services available for them. Outcome measures include carers’ subjective burden, depressive symptoms, health-related quality of life, social support, caregiving self-efficacy, and care recipients’ difficult behaviours and competence in activities of daily living at 3, 9 and 15 months after baseline. The potential cost-effectiveness of the ITBCS compared with usual care will be assessed as well.

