### Intervention

Three theoretical approaches inform the ITBCS program. First, Ruth Cohn’s theme-centered interaction (TCI) model that emphasizes partnerships with family caregivers to improve their self-management of dementia at home and thereby reduce difficult behaviours of people with dementia [30]. Second, the perspective of systemic therapy that emphasizes psychological burdens should not just be considered at the individual level, but also at the system level where people with dementia are cared for [31]. Third, the principles of behavioral therapy point out that difficult behaviours of people with dementia could be triggered by the behaviour of their family caregivers [32]. Therefore, coaching caregivers to apply evidence-based care approaches can reduce difficult behaviours and caregiver burdens. The ITBCS program is designed to enhance family caregiver coping abilities through active problem-solving and facilitating positive changes within the family system via individual phone care support sessions.

Participants will be enrolled for 15 months. For intervention and control groups, there are four assessment time points: the beginning of the study (T-0) and at 3 months after baseline (T1), 9 months after baseline (T2), and 15 months after baseline (T-3). The assessment time points and intervention activities for both groups is shown in Table 1. The ITBCS program includes two major components: intensive ITBCS intervention and telephone consultations at the maintenance phase.

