#### Primary outcomes

The primary outcome measure is family caregivers’ perceived burden at 15 months follow-up adjusted for baseline value.

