#### Economic evaluation

***Quality-adjusted life-years (QALYs):*** The SF-12 will be used to collect data for the QALYs calculation. QALYs will be calculated using the SF-6D preference to estimate the utilities based scoring algorithm developed by Brazier and colleagues [40].
***Health care utilization:*** This proposed study will measure the direct costs related to the family caregiver’s situation and people with dementia. Direct costs will include medications, admissions to hospitals, admission to other institutions, and the number of consultations with health professionals (GP, RN, medical specialist, physiotherapist, etc.). Indirect costs are reduced efficiency at work (presenteeism) and the productivity loss caused by work absenteeism.
***Time spent on caregiving:*** Caregivers will be asked to estimate the total hours spent on providing care for people with dementia in the past week. In addition to this, information of the availability of other informal caregivers will be collected by the research team. The total time the primary family caregiver and other informal caregivers spent on providing care will be recorded and calculated.

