### Statistical methods

All data will be double entered into an Excel database on two separate occasions and exported to SPSS software 25.0 for analysis. Internal consistency of the seven instruments will be tested using Cronbach’s alpha coefficient. For the pilot study, paired *t* tests will be conducted to evaluate whether any differences occurred in participants on the seven outcome variables pre- and post-intervention. The research team will perform all analyses of the cluster RCT study based on the intention to treat principle. Baseline data between the experimental and control group will be compared. Missing data will be imputed if deemed necessary. The most appropriate imputation methods will be decided based on the amount and pattern of missing data. A mixed effect model, which takes into account the repeated measurement of outcomes, will be conducted to analyse the primary outcome. The mixed effect model will include treatment, time, and interaction between time and treatment as the fixed effect, baseline measurement of outcome as the covariate, and subject as a random effect. The treatment difference and its 95% confidence interval (CI) will be derived from the mixed effect model. Moreover, adjusted treatment difference will be derived by adding the pre-specified covariates into the mixed effect model. All other outcomes (CES-D, SF-12, SSRS, RSCSE, NPI-Q and DAD) will be analyzed separately using this general framework.

Cost-effectiveness analyses (CEA) and cost-utility analyses (CUA) will be conducted. The difference of total costs among scenarios will first be calculated, which will be further divided by the difference in average effect sizes to estimate the incremental cost-effectiveness ratio. Inflation correction is not necessary as we will evaluate the costs covering 9 months. Multiple imputation methods will be applied to deal with the missing data in the follow-up measurements. A 95% confidence interval of the mean difference in the treatment groups’ total costs will be calculated. Cost-effectiveness acceptability curves will indicate the cost-effectiveness comparison between the ITBCS program and the usual care, with a range of different ceiling ratios presenting decision uncertainties. Furthermore, sensitivity analyses to test the robustness, such as scenarios that vary key variables will be conducted.

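### Costs are evaluated over 9 months in a 15-month trial, and no common horizon is set for costs, effects and QALYs

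*Protocol article*

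**What the plan says.** On costs, the Statistical methods section states: "Inflation correction is not necessary as we will evaluate the costs covering 9 months". The same paragraph takes the difference in total costs, "which will be further divided by the difference in average effect sizes to estimate the incremental cost-effectiveness ratio", and gives no time point for that effect difference.

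The Economic evaluation section says "The SF-12 will be used to collect data for the QALYs calculation", scored through the SF-6D, and gives no QALY horizon. Its cost list goes beyond programme delivery: "Direct costs will include medications, admissions to hospitals, admission to other institutions, and the number of consultations with health professionals". It also counts productivity loss.

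The design runs longer. Under Intervention: "Participants will be enrolled for 15 months", with assessments at baseline and "at 3 months after baseline (T1), 9 months after baseline (T2), and 15 months after baseline (T-3". The abstract lists health-related quality of life among the outcomes measured at 3, 9 and 15 months. Under Primary outcomes, the endpoint is "perceived burden at 15 months follow-up adjusted for baseline value".

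**The concern.** The cost period is six months shorter than the trial, and the article gives no reason. An ICER can be interpreted only if its numerator and denominator cover the same period. Here the numerator is fixed at 9 months and the denominator is left open, in a trial whose main endpoint is at 15 months.

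The missing half-year bears on the economic question. The Background cites lower institutionalisation as a source of economic benefit from caregiver support, and admissions to hospitals and other institutions are on the cost list. Such costs or savings, and any fading of the effect once regular contact ends, could appear after month 9. The 9-month figure is also the only ground given for leaving prices uncorrected.

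**Working it through.** **1. Where 9 months could come from.** The abstract describes "a 3-month intensive telephone-based care support intervention followed by telephone-based follow-up consultations for 6 months". 3 + 6 = 9 months, which reproduces the stated cost period and coincides with the T-2 visit. The article does not say that this is the reason.

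**2. Share of follow-up without costs.** Follow-up is 15 months and costs cover 9, taken here as months 0 to 9. (15 − 9)/15 = 6/15 = 0.40, or 40%.

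**3. Check on the timeline.** The Variables and measurements section counts T-2 and T-3 from after the intervention rather than from baseline. Read literally, follow-up would end at 3 + 15 = 18 or 9 + 15 = 24 months, and the uncosted share would be (18 − 9)/18 = 50% or (24 − 9)/24 = 62.5%. The Intervention section and the abstract both count from baseline. The Limitations section, with 12 months of follow-up after completion, agrees if counted from the end of the intensive phase: 3 + 12 = 15. I use 15 months, so 40% is the lowest of the three figures.

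**4. Reading A: costs to month 9, QALYs to month 15.** The documents give no utility values, so this is only an illustration. Assume a utility gain *u* that rises linearly from 0 at baseline to *u* at month 3 and stays constant to month 9.
- Gain to month 9: (½ × 3 + 6) × *u*/12 = 7.5*u*/12 = 0.625*u*.
- Gain to month 15 if the effect is sustained: (½ × 3 + 12) × *u*/12 = 13.5*u*/12 = 1.125*u*. Ratio 13.5/7.5 = 1.8.
- Gain to month 15 if the effect fades linearly to zero between months 9 and 15: (7.5 + ½ × 6) × *u*/12 = 10.5*u*/12 = 0.875*u*. Ratio 10.5/7.5 = 1.4.

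For the same 9-month cost difference, using 15-month QALYs would divide the ICER by 1.4 to 1.8 under these assumptions. This is not the net error against a full 15-month analysis, because the cost difference in months 9 to 15 is unknown and may have either sign.

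**5. Reading B: costs and effects both to month 9.** The periods match, but six months of outcome and SF-12 data and the primary time point do not enter the economic result.

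**6. Are months 9 to 15 still a randomised comparison?** Yes. The section on treatment as usual has control participants offered the programme only after the study is complete, so the arms remain comparable to month 15.

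**7. Prices.** A 15-month horizon exceeds one year, so the stated reason for no correction does not carry over. The documents give no inflation rate. Only months 13 to 15 lie beyond the first year, so I take the correction to be small; the horizon is the main issue.

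**The case against.** The strongest reply is that 9 months is a deliberate within-programme horizon. It equals the delivery period and falls on a visit, and nothing obliges a secondary economic evaluation to share the clinical endpoint's time point. The time points of effects and QALYs may be set in an analysis plan that is not shown.

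Part of this stands. A 9-month horizon is a recognised, if limited, option, and silence on the effect time point alone would be no fault in a condensed article. But the article does not leave the cost horizon open. It states a figure that differs from the trial's own length, rests a decision about prices on it, and gives no reason. An analysis plan with a 15-month horizon would have to contradict it.

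A reader might infer more than the documents support:
- **That the ICER does mix two horizons.** This is not shown, because no time point is given for effects or QALYs.
- **That cost data to month 15 are collected and then discarded.** Collection to month 15 is stated for outcomes, including the SF-12. The schedule for resource use is not visible; it may be in Table 1, which is not shown.
- **That the 9-month window holds all programme effort.** Field officers are trained before recruitment, and the timing of the compliance calls C-1 to C-3 cannot be seen.
- **That the 40% measures bias.** It is a share of calendar time.

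**Conclusion.** The point holds as an unexplained conflict between a 9-month cost period and a 15-month design. Each available reading weakens the economic result: Reading A gives an ICER whose two parts cover different periods, and Reading B gives one that leaves out 6 of 15 months and the primary time point. Confidence in the discrepancy itself is high. Its effect on the ICER has unknown direction and size, and the factors of 1.4 to 1.8 rest on an assumed utility curve and on Reading A being the one applied. The analysis of caregiver burden is not touched. The change should be made, but the trial's main conclusion does not depend on it.

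**What to change.** In the Statistical methods section, set one horizon for costs, effects and QALYs:
- Base case of 15 months, with QALYs as the area under the SF-6D curve over T-0, T-1, T-2 and T-3, and the effect difference taken over the same period.
- Replace the inflation sentence with a statement that all prices are expressed in one base year.
- Report the 9-month within-programme result as a sensitivity analysis.

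The cost is a wording change and modest extra analysis. If resource use is not already planned for T-3, those questions must be added at that visit, with some added burden on caregivers and assessors. The visit already exists, and the Trial status section put the start of recruitment after publication, at the end of December 2021, so the change could be made before any data were collected. Resource use not asked about at T-3 would be hard to recover later.

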### Trial status

Most of the field research activities of our team have been restricted because of the COVID-19, which has delayed the project implementation. The paricipants recruitment will start by the end of December 2021.

## Discussion

It is urgent to develop feasible and cost-effective programs that satisfy the needs of family caregivers of people with dementia across the course of dementia in rural areas in China, improving quality of life and health-related outcomes for family caregivers and care recipients [3, 6, 7]. Effective interventions tailored to rural health resources and rural family caregivers’ knowledge and skills, education level, and cultural values are much needed in dementia care to generate research evidence to inform policy, resource, and practice development in dementia care in rural China. To our knowledge, this study is the first to examine the efficacy and cost-effectiveness of an evidence-based ITBCS through a cluster RCT in China.

The development of the ITBCS program is based on the successful telephone-based multi-component intervention (TALKING TIME) which is designed to enhance family caregiver coping abilities through facilitating positive changes and active problem-solving within the family system via individual phone care support sessions [15, 32]. This proposed study will be the first to adapt TALKING TIME into the Chinese context and to examine the feasibility, efficacy, and cost effectiveness of this program through a cluster RCT in Central South China. The findings are expected to contribute to the development of dementia health care services in China.

There will be a number of challenges when implementing the trial. Community health professionals in rural China are less educated and skilled than their counterparts in urban cities. In such a situation, the project field officers will be supported in the project by skilled professionals to ensure scaling-up of the present study and future sustainability. The training materials and information booklet will be developed to ensure easy understanding. The project team will train a replacement project field officer if one is unable to continue their role due to unforeseen reasons. A WeChat group will be set up for each group of project field officers to raise concerns and ask questions. The project team will be available to answer questions and provide advice regarding ITBCS delivery. Another challenge is how to ensure high compliance with the intervention and retain participants. Multiple strategies will be applied to maximize compliance in this population, for example, the information booklet, reminder calls, telephone consultations, and cash-based gifts as incentives. Despite many challenges, if proved effective, this study would provide the results of the efficacy of the ITBCS program and be a basis for the ITBCS program dissemination to other rural communities and thereby reducing the disease burden of dementia in China.

### Limitations

This proposed study has some limitations. Firstly, the reliance on self-report data and.

the limited geographical reach of the present proposed study limits its generalizability.

Any long-term effects of the ITBCS program on the outcomes will be difficult to show because of the limited timeframe of this proposed project. However, the sample size calculated is theoretically sufficient to detect a meaningful statistical difference. We also use the cluster randomization technique to maximize population representation and increase follow-up to 12 months after intervention completion. We have also included health outcomes of people with dementia to minimize the self-report bias of family caregivers.

### Significance

The WHO urges all countries to make dementia a public health priority, develop programs to improve family caregivers’ and care recipients’ quality of life, and provide equitable support for family caregivers across rural and urban areas [8, 9]. The proposed study aims to develop and provide appropriate and meaningful individualized care support for family caregivers of people with dementia in rural China in a cost-effective way. If proved effective, the present proposed interdisciplinary study will potentially improve the quality of life and health outcomes for millions of people with dementia and their family caregivers. Moreover, in addition to the benefits from the findings, our study provides feasible solutions for intervention program maintenance by building local capacity. The rural community health professionals selected as local project field officers will be trained in dementia care intervention skills, which will facilitate the dissemination of the dementia care intervention program to other communities in the future using a train-the-trainer model.

## Data Availability

All data collected during the present study will only be accessible to the researchers. Public access to the study-related data will be available upon approval via the Chinese clinical trial registry.

## Abbreviations

BPSD: Behavioral and psychological symptoms of dementia
CEA: Cost-effectiveness analysis
CES-D: Centre for Epidemiologic Studies depression scale
CI: Confidence interval
CUA: Cost-utility analysis
DAD: Disability assessment for dementia
ICC: Intra-class correlation coefficient
ICERs: Incremental cost-effectives ratios
ITBCS: Individualized telephone-based care support
SSRS: Social support rating scale
NPI-Q: Neuropsychiatric inventory-Q
QALYs: Quality-adjusted life-years
RCT: Randomized controlled trial
RSCSE: Revised scale for caregiving self-efficacy
SF-12: 12-Item short-form health survey
TCI: Theme-centered interaction
ZBI: Zarit burden interview
